**Fig. 1 Fig1:**
[figure not shown]
Trial flow diagram

### Outcome measures

The following primary and secondary, self-report outcome measures will be administered by blinded research assistants at baseline and 3 and 6 months.

#### Primary outcome measures: pain intensity

Our primary outcome measure will be pain intensity measured at 6 months using a Visual Analogue Scale (VAS) of 100 mm. However, the Descriptor Differential Scale, a valid measure of pain intensity, will also be assessed [25]. The Descriptor Differential Scale has been used in a previous trial of antidepressants in low back pain [15], enabling calculation of study sample size and comparison of results.

#### Secondary outcome measures: disability, work absenteeism and hindrance in work performance

Disability will be assessed using the Roland Morris Disability Questionnaire [26], which is a validated instrument designed to assess self-rated disability caused by low back pain.

We will examine absenteeism and hindrance in performance of paid and unpaid work using The Short Form Health and Labour questionnaire (SFHLQ). The SFHLQ is a validated questionnaire which examines work absenteeism and hindrance in performance of paid and unpaid work in relation to injury or sickness [27].

### Other measures

Global improvement: a 6-point scale, ranging from 'no change' to a 'great deal better' will be used to assess global improvement [28].

General health status will be measured using the EuroQol, 5 dimensions instrument (EQ-5D-5 L) [29].

Depression: severity of mood symptoms will be assessed using the Beck Depression Inventory [30].

Fear of movement/(re)injury will be examined using the 17-item Tampa Scale [31].

### Potential explanatory factors

#### Anthropometry

Height (stadiometer), weight (electric scales) and Body Mass Index (height/weight^2^) will be measured at baseline.

#### Physical activity

The International Physical Activity Questionnaire short version [32] will be used at baseline, and 3 and 6 months.

#### Concomitant medication use

The use of non-opioid analgesics and non-steroidal anti-inflammatory drugs (NSAIDs) will be allowed during the trial. The randomisation process is the most effective method for ensuring that the two groups are as similar as possible with respect to known confounders and unknown potential confounders including treatments. We will also adjust for medication use in the analyses.

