### Sample size calculation

#### Reduction in pain intensity

A previous clinical trial of TCAs in individuals with chronic low back pain reported the mean (standard deviation (SD)) pain scores measured on the VAS to reduce to 5.70 (2.43) in the placebo group (*n* = 48) [34]. With *n* = 56 in each arm of the study, we have 90 % power to detect a difference of 1.5 (i.e. VAS to reduce to 4.20 (2.43) in the treatment group), which reflects the minimum clinically significant reduction in pain intensity (*α* = 0.05, two-sided significance).

In a recent study of individuals with low back pain, the control group (*n* = 22) had a pain score that reduced to a mean (SD) = 6.2 (2.8) on the Descriptor Differential Scale following treatment, while the pain score of the treatment group (TCA) (*n* = 19) reduced to a mean (SD) score = 4.5 (2.6) [15]. With an *α* = 0.05 and *n* = 60 in each arm of the study, we have 90 % power to detect a difference of this size (1.7), which reflects clinically significant reductions in pain intensity from ‘moderate’ to ‘mild’ or from ‘strong’ to ‘moderate’, which is equivalent to a decrease of 2 units (17 %) on the Descriptor Differential Scale (0–12 per descriptor) [35].

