### Statistical analysis

Summary statistics comparing randomised arms at baseline will be tabulated. Intention-to-treat analyses of primary and secondary continuous outcomes will be performed by linear regression adjusting for the baseline of the outcome variable where relevant. Logistic regression will be performed for binary outcomes. Adjustment for imbalanced baseline factors, including the presence of symptoms other than low back pain, will be performed as supplementary analyses. Analyses of treatment efficacy will be done by censoring individuals at the time of any protocol deviation and developing a model for the probability of deviation, followed by weighted analyses using only the uncensored individuals where the weights are the inverse probability of censoring. This produces estimates of treatment effect as if there was full compliance with the protocol in this RCT and is far preferable to per-protocol analyses based on (unweighted) observed compliance [38]. This RCT is well-placed to model noncompliance with frequent monitoring for adverse events and resultant prognostic information.

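### The plan promises to adjust the analyses for medication use in a section about analgesics taken during the trial; such an adjustment does not give the intention-to-treat effect, and it is not reconciled with the Statistical analysis section

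*Protocol article*

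**What the plan says.** The section Concomitant medication use (under Potential explanatory factors) makes three statements in order:

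- "The use of non-opioid analgesics and non-steroidal anti-inflammatory drugs (NSAIDs) will be allowed during the trial".
- Randomisation is the best way to make the groups alike on "known confounders and unknown potential confounders including treatments".
- "We will also adjust for medication use in the analyses".

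The last sentence names no time point and no particular analysis.

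The Statistical analysis section describes the main model: "Intention-to-treat analyses of primary and secondary continuous outcomes will be performed by linear regression adjusting for the baseline of the outcome variable where relevant". The only other covariate adjustment it names is this: "Adjustment for imbalanced baseline factors, including the presence of symptoms other than low back pain, will be performed as supplementary analyses". Medication use appears in neither sentence.

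The outcome concerned is pain: "Our primary outcome measure will be pain intensity measured at 6 months using a Visual Analogue Scale (VAS) of 100 mm".

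**The concern.** Patients take analgesics because they hurt. If amitriptyline relieves pain, as the trial hypothesises, participants on it may take fewer analgesics. On-trial use is then a consequence of treatment and not a confounder of it. Putting it in the regression does two things. It removes any part of the effect that runs through analgesic use. It also compares participants matched on a variable that depends on both treatment and unmeasured causes of pain, which opens a non-causal path between treatment and outcome.

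The stated rationale does not help. Randomisation balances what exists before it, not what participants take afterwards in response to how they feel.

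At stake is what the reported difference means. The article says that a finding of no effect would be strong evidence for reconsidering the drug's use, so an adjustment that can shift the estimate matters. There is also an open choice: an analyst could report the estimate with or without medication use and cite the protocol for either.

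**Working it through.** **1. The plan's own figure.** The sample size section says "we have 90 % power to detect a difference of 1.5" with 56 per arm, SD 2.43 and two-sided α = 0.05.

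n per arm = 2 (1.960 + 1.282)² × (2.43 / 1.5)² = 55.2, rounded up to 56. This reproduces. The general statement of 60 per arm for 0.60 SD also holds: 2 (1.960 + 1.282)² / 0.60² = 58.4, so 59 suffices. Then 60 / 0.8 = 75 per arm, 150 in total. None of this depends on the medication covariate.

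**2. The two sections side by side.**

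| | Concomitant medication use | Statistical analysis |
|---|---|---|
| Adjusts for | medication use | baseline value of the outcome; imbalanced baseline factors as supplementary |
| Timing | not stated; the section opens with drugs taken during the trial | baseline |
| Which analyses | not stated | intention-to-treat, then supplementary |

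Both cannot describe the same primary model.

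**3. How far the estimate could move.** The document has no figures on analgesic use, so this part is illustrative. Taken from the plan: difference 1.5 (read as a 0–10 scale) and SD 2.43. Everything else is assumed. In each simulation (1,000,000 participants per scenario) the linear regression of 6-month pain on arm and baseline (ITT) is compared with the same model plus on-trial analgesic use M (adjusted).

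*Model A: use follows mid-trial pain.* A is the arm; B, U and e are independent standard normals.

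- Mid-trial pain = 2.43 (0.5B + 0.6U) − 1.5A
- Analgesic-free 6-month pain = 2.43 (0.5B + 0.6U + √0.39 e) − 1.5A
- logit P(M = 1) = 0.45 + s × mid-trial pain − dA
- Observed score = analgesic-free 6-month pain − gM

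Here d is any effect of treatment on analgesic use other than through pain, and g is the pain relief from the analgesic.

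| s | d | Use, control / active | g = 0: ITT → adjusted (ratio) | g = 1: ITT → adjusted (ratio) |
|---|---|---|---|---|
| 0.3 | 0 | 0.60 / 0.50 | −1.50 → −1.44 (0.96) | −1.40 → −1.44 (1.03) |
| 0.6 | 0 | 0.59 / 0.41 | −1.51 → −1.31 (0.87) | −1.32 → −1.30 (0.99) |
| 0.3 | 0.5 | 0.60 / 0.39 | −1.50 → −1.37 (0.91) | −1.28 → −1.37 (1.06) |
| 0.6 | 0.5 | 0.59 / 0.32 | −1.50 → −1.20 (0.80) | −1.22 → −1.19 (0.98) |
| 0.3 | 1.0 | 0.60 / 0.28 | −1.51 → −1.31 (0.87) | −1.18 → −1.31 (1.10) |
| 0.6 | 1.0 | 0.59 / 0.24 | −1.50 → −1.12 (0.74) | −1.15 → −1.11 (0.97) |

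The analgesic-free effect is −1.50 by construction in every row, and the adjusted coefficient does not recover it in any. With g = 1 it generally misses the ITT effect as well.

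*Model B: use follows concurrent pain.* Baseline correlation 0.45; odds ratio for use per SD of pain; use 55–57% on control and 38–47% on active.

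| Odds ratio | Ratio, g = 0 | Ratio, g = 1 | Ratio, g = 1.5 |
|---|---|---|---|
| 2 | 0.92 (−1.38) | 0.985 | 1.02 |
| 3 | 0.84 (−1.26) | 0.92 | 0.97 |
| 5 | 0.75 (−1.12) | 0.84 | 0.90 |

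**4. No effect on pain.** In model A with the 1.5 set to zero, both estimates are 0 if treatment leaves analgesic use alone. If treatment lowers use by another route and g = 0, the ITT effect is 0 but the adjusted one is +0.06 to +0.22.

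**5. Baseline use instead.** Adjusting for pre-randomisation use left the effect unchanged in every model B scenario.

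**The case against.** The strongest reply is that the primary model is not shown to be affected. The Statistical analysis section says the intention-to-treat analyses "will be performed by linear regression adjusting for the baseline of the outcome variable where relevant", and medication use is not there. That stands. A reader might infer that the primary result will be adjusted for on-trial analgesics; the document does not establish this, because the medication sentence does not say which analyses it covers.

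Second, the sentence gives no time point. The preceding sentence, on randomisation, fits treatment already in use at entry, and baseline use would be a harmless covariate. This stands only in part. The heading and opening sentence concern drugs taken during the trial, and the article writes baseline elsewhere when it means baseline. Leaving covariate detail to a fuller document would be normal; giving an unqualified commitment with a mistaken rationale is a different matter.

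Third, a reader might infer that adjustment must pull the estimate towards no effect. The working does not support that. Losses of up to about 26% arise when analgesics are assumed not to change the score, an odd assumption for pain relief. Once they lower pain, the ratio can reach or exceed 1, although attenuation can also persist. Precision matters too: adjustment reduces residual variance. In the harshest model B case (odds ratio 5, g = 0), with 120 completers, the expected z falls from about 3.78 to 3.21. Nominal power is then about Φ(3.78 − 1.96) = 0.97 against Φ(3.21 − 1.96) = 0.89, a real loss but not a collapse.

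**Conclusion.** The sentence is wrong as written. In its place it commits the analyses to a covariate that arises after randomisation and that treatment can change through pain. An analysis following it would not estimate the intention-to-treat effect promised in the Statistical analysis section. Without further assumptions it would not be a valid estimate of the effect without analgesics either. That conclusion rests on reasoning about timing and needs no simulation.

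The consequence for the primary result is conditional on two things: that the sentence applies to the primary model, and that treatment changes analgesic use. The document settles neither. Under the assumed inputs the adjusted estimate was about 0.74 to 1.10 times the ITT estimate, so neither the size nor the direction of the distortion can be stated as fact. If treatment leaves analgesic use unchanged, there is none.

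**What to change.** Replace the last sentence of Concomitant medication use with wording such as:

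> Primary and secondary intention-to-treat analyses will not adjust for medication used after randomisation. Analgesic/NSAID use before randomisation may be a prespecified covariate. On-trial use will be reported by arm.

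Then make the Statistical analysis section agree: either list pre-randomisation use as a covariate or state that medication use is not in the model.

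If the effect without concomitant analgesics is also of interest, define it as a separate supplementary analysis with its own stated method. The planned inverse-probability weighting does not supply it as it stands. That analysis censors at protocol deviations, and taking a permitted analgesic is not one.

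The cost is a sentence in each section, with no change to the 150 participants. The article does not say when or how analgesic use is recorded, so the team should confirm that both pre-randomisation and on-trial use are captured.

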#### Compensation status

For each individual we will record whether their back pain is associated with a compensation claim, and if so the nature of the claim, including the type, duration, items approved and associated costs.

#### Monitoring

Adverse events will be monitored on a monthly basis over the phone using a validated questionnaire, the UKU Side Effects Rating Scale [33]. This questionnaire involves a standardised, physician-administered interview for assessing the severity and impact of side effects of psychotropic drugs on daily function. The participants will be requested to report any adverse events to the research staff spontaneously. Details of major adverse events and their relationship with study intervention will be recorded and reported to the Ethics Committees. The participants’ physician will also be notified of their inclusion in the trial.

### Sample size calculation

#### Reduction in pain intensity

A previous clinical trial of TCAs in individuals with chronic low back pain reported the mean (standard deviation (SD)) pain scores measured on the VAS to reduce to 5.70 (2.43) in the placebo group (*n* = 48) [34]. With *n* = 56 in each arm of the study, we have 90 % power to detect a difference of 1.5 (i.e. VAS to reduce to 4.20 (2.43) in the treatment group), which reflects the minimum clinically significant reduction in pain intensity (*α* = 0.05, two-sided significance).

In a recent study of individuals with low back pain, the control group (*n* = 22) had a pain score that reduced to a mean (SD) = 6.2 (2.8) on the Descriptor Differential Scale following treatment, while the pain score of the treatment group (TCA) (*n* = 19) reduced to a mean (SD) score = 4.5 (2.6) [15]. With an *α* = 0.05 and *n* = 60 in each arm of the study, we have 90 % power to detect a difference of this size (1.7), which reflects clinically significant reductions in pain intensity from ‘moderate’ to ‘mild’ or from ‘strong’ to ‘moderate’, which is equivalent to a decrease of 2 units (17 %) on the Descriptor Differential Scale (0–12 per descriptor) [35].

#### Improvement in disability

With 60 in each arm of the study, we will have 90 % power to detect a clinically relevant difference in disability (improvement of 13–16 % in disability or 3–4 points on the 24-point Roland Morris Disability Questionnaire after 26 weeks [36]) (*α* = 0.05, two-sided significance), which corresponds to a significant improvement in key functional activities, including walking and dressing.

More generally, with 60 per arm we have 90 % power to detect a difference of 0.60 SDs. With our primarily analyses involving adjustment for the baseline value of the outcome, we will have greater than 90 % power according to the size of the baseline-follow-up correlation. Given our previous experience in such studies we expect a maximum dropout rate of 20 % so we will recruit a total of 150 (75 in each arm of the study) [37].

### Statistical analysis

Summary statistics comparing randomised arms at baseline will be tabulated. Intention-to-treat analyses of primary and secondary continuous outcomes will be performed by linear regression adjusting for the baseline of the outcome variable where relevant. Logistic regression will be performed for binary outcomes. Adjustment for imbalanced baseline factors, including the presence of symptoms other than low back pain, will be performed as supplementary analyses. Analyses of treatment efficacy will be done by censoring individuals at the time of any protocol deviation and developing a model for the probability of deviation, followed by weighted analyses using only the uncensored individuals where the weights are the inverse probability of censoring. This produces estimates of treatment effect as if there was full compliance with the protocol in this RCT and is far preferable to per-protocol analyses based on (unweighted) observed compliance [38]. This RCT is well-placed to model noncompliance with frequent monitoring for adverse events and resultant prognostic information.

### Data integrity and management

All collected data will be recorded using Case Report Forms or questionnaires and stored in a locked area in the Department of Epidemiology and Preventive Medicine at Monash University with secured and restricted access. The electronic data will be stored in a password-protected database with secured and restricted access. All data collected will be kept strictly confidential. Data transfer will be encrypted with all data deidentified. Only research personnel on the project will have access to the study data.

### Withdrawal

If participants withdraw before completion of the study, the reason and date will be recorded and participants will be asked if they can complete the remaining outcome measures.

### Monitoring

The principal investigators will monitor the conduct and progress of the project and ensure that all trial procedures are compliant with the trial protocol. The research team will have regular meetings to ensure efficient study execution and ongoing monitoring of adverse events.

## Discussion

We have proposed to conduct a pragmatic, double-blind, randomised, placebo-controlled trial to investigate whether low-dose amitriptyline is more effective than placebo in the management of pain in individuals with chronic low back pain. We will also investigate whether lose-dose amitriptyline is more effective than placebo in improving disability and minimising absenteeism and hindrance with performance of paid/unpaid work. If amitriptyline is found to be effective, it will provide high-quality evidence for this therapeutic approach to the management of chronic low back pain.

This current trial of amitriptyline for chronic low back pain was designed to address some of the limitations of previous RCTs which have been identified in meta-analyses. The most up-to-date meta-analyses by the Cochrane collaboration reported that a qualitative analysis of the trials with a low risk of bias found conflicting evidence regarding the effectiveness of antidepressants in the reduction of pain for individuals with chronic low-back pain, while a meta-analysis of six trials showed no difference in pain relief between antidepressants and placebo [14]. The review highlighted a number of limitations including a paucity of trials that examined antidepressants for the treatment of pain, in particular those which used a low-dose antidepressant. Moreover, small sample sizes, which can result in insufficient statistical power to detect clinically relevant effects, was a key limitation. Of the six trials identified in the Cochrane meta-analysis examining the effect of low-and high-dose antidepressants on pain, study populations ranged from 18 to 92 (randomised) subjects. In this current clinical trial we aim to recruit 150 subjects with chronic low back pain. If successful, it will be the largest trial of an antidepressant for the treatment of pain in participants with low back pain to date. A further methodological issue that was reported was the short follow-up periods of the trials [14]. These periods were generally between 6 and 8 weeks; however, one study followed up participants only until 4 weeks [39], while a single study extended to 12 weeks [15]. We have selected to follow-up participants over 6 months to enable the efficacy of the low-dose antidepressants to be examined over a longer time period.

Previous trials that have examined the efficacy of antidepressants for treating pain in low back pain have varied in both the percentage of participants recruited with and without depression and the severity of depression of the included participants. While one study specifically selected participants with overt symptoms of depression [34] and two studies have included a mix of participants with and without depression [39, 40], two studies excluded individuals with major depression [15, 41] and, in a further study, it was unclear whether participants had depression [42]. We have chosen to exclude potential participants with depression or psychosis to allow us to examine the effectiveness of low-dose amitriptyline specifically on pain. Finally, we have chosen to use an active placebo, benztropine mesylate. Only two of the previous studies used an active placebo, with the remaining studies selecting a standard, inactive placebo. The benefit of using benztropine mesylate is that it mimics the side-effects of amitriptyline and assists with blinding of participants.

This trial has several potential limitations that need to be considered. Given that we are examining the effectiveness of low-dose amitriptyline, which is a TCA, it is not possible to directly extrapolate the findings to higher doses of TCAs or other types of antidepressants. While a variety of different types of antidepressants have been examined in the management of low back pain, much of the investigation has focused on TCAs and SSRIs. TCAs and SSRIs block the absorption of the chemicals or neurotransmitters, serotonin and/or noradrenaline, at the spine and midbrain [6]. There is preliminary evidence to suggest that low-dose TCAs produce greater reduction in pain compared with SSRIs and placebo. For instance, a study by Atkinson [15], which performed a head-to-head comparison for TCAs and SSRIs, showed an effect size of 0.31 (−0.23, 0.87) for fluoxetine (SSRI) and −0.62 (1.24, −0.01) for desipramine (TCA). This provides preliminary evidence suggesting that low-dose TCAs produce greater reduction in pain compared with placebo and SSRIs. However, this is still not proven in the treatment of low back pain as meta-analyses show no significant differences in pain between the TCA and SSRI treatment groups [14].

The current trial will involve the recruitment of participants with chronic, nonspecific low back pain. While this means that our population sample has the potential to be heterogeneous in nature, the participants recruited will represent a distinct clinical entity; that is they will have pain that has been present for longer than 3 months, their pain will be of no known cause and participants will have no diagnosed psychosis or depression. A further limitation of this trial relates to examining the adverse events associated with the use of low-dose antidepressants. While in our evaluation of the effectiveness of amitriptyline we will record the type, frequency and severity of adverse events that occur during the trial, the study is not designed to evaluate adverse events and prospective cohort studies with larger sample sizes are needed to examine the incidence of adverse events.

In summary, low back pain is the leading cause of disability worldwide, but effective treatment approaches are limited. Low-dose antidepressants are commonly used in clinical practice to treat pain in individuals with chronic low back pain; however, their use is unproven. This RCT will provide high-quality evidence to investigate whether low-dose amitriptyline is an effective treatment in the management of low back pain. If amitriptyline is found to be effective, it could be used to reduce pain, disability and work absenteeism and hindrance of work performance in individuals with chronic low back pain, and in turn, reduce the need for treatments and surgery that result in substantial costs to the community.

